### Definition of terms

Important variables are defined according to the researchers’ operation used in the research and all definitions are annexed in Appendix 2.

### Sample size determination

#### Sample size for TB diagnosis delay among tuberculosis patients

To estimate the effect of integrating traditional care with modern care on diagnosis delay, the sample size will be calculated using the two-sample comparison of proportions formula in STATA version 16. A chi-squared test with two independent samples will be used to calculate the sample size using diagnosis delay. By considering the previous study conducted in the Amhara region with the proportion of diagnosis delay P1 = 59.9% [24] and by assuming that the effect of the intervention on diagnosis delay decreased by 14% in the intervention group as compared to the control, P2 = 45.9%. By considering the probability of a type 1 error of 0.05, 95% CI, power of 80%, and a 10% non-response rate, the total sample size will be 438. Since the study is a multicenter, individually randomized trial, the design effect will be used. According to the multicenter design effect formula, the design effect formula, the $$\mathrm{design\ effect}=\frac{\upsigma {e}^{2}}{\sigma {e}^{2}+\sigma {B}^{2}}$$ = 1 − *ρ*. The majority of formulas applied to multicenter designs have a better relative accuracy (ICC less than 0.052) for designs including more than 10 centers. Assuming that randomized will be balanced and stratified on centers that have equal group sizes [37], assuming the variation between the centers will be 0.05, the design effect = 1 – *ρ* = 0.95. Therefore, the final sample size is calculated as sample size * design effect; 438 * 0.95 = 416 (208 for each arm).

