#### Phase 4: The end-line evaluation

End-line outcome assessment will be done by trained assessors. The comparison will be done between the end-line and baseline outcomes (case detection rate, cost of TB, and diagnosis delay) between the intervention and control groups.

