### Control groups

The control sites will follow the existing passive case-finding system (self-referral patients to nearby health facilities that use the same national guidelines to treat TB). The findings obtained from the control groups will be compared with those obtained from the intervention groups. Finally, changes between the two groups will be assessed and concluded.

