#### Sample size calculation for cost of TB care among tuberculosis patients

To estimate the effect of integrating traditional care with modern care on the cost of TB care will be considered. The sample size will be calculated by using the two-sample comparison of proportions formula using STATA version 16. A chi-squared of the two independent samples will be used to calculate the sample size using household catastrophic cost incurred that catastrophic household expenditure of P1 = 40% [38] and assuming that the effect of the intervention on the cost of TB care decreased by 13% in the intervention group as compared to the control, P2 = 27% and using, 95% CI, power of 80%, and a type I error of 0.05, considering 10% non-response rate, the final sample size was 453. Since the study is a multicenter individually randomized trial, design effect will be used. According to the multicenter design effect formula, design effect formula is $$\mathrm{design\ effect}=\frac{\upsigma {e}^{2}}{\sigma {e}^{2}+\sigma {B}^{2}}$$ = 1 − *ρ*. The majority of formulas applied on multicenter design with better accuracy relative difference (ICC lesser than 0.052) for designs including more than 10 centers. Assuming that randomization will be balanced and stratified based on centers that have equal group sizes [37]. Assuming the variation between the centers is 0.05, design effect = 1 – *ρ* = 0.95. Therefore, the final sample size will be calculated as sample size * design effect 453 * 0.95 = 428 (214 in the intervention arm and 214 in the control arm).

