### Data collection

Data will be collected on the dependent variables (i.e., case detection, diagnosis delay, and cost of TB care) and independent variables (i.e., socio-demographic, health-seeking behavior variables, patient knowledge of TB, healthcare accessibility, distance, contact history, and support). Secondary data will be collected from the patient’s medical records, and primary data will be collected using a structured questionnaire adapted from previous literature. The structured questionnaire is composed of socio-demographic and economic factors, health-seeking behaviors, patient knowledge, service accessibility, stigma, contact history, the catastrophic cost of TB, diagnosis delay, and healthcare initiation. The questionnaire will be translated into the national language (Amharic) spoken by almost all residents in the study area. The data will be collected using face-to-face interview questionnaires. The data will be collected by BSc nurses or public health officers who had data collection experience. Nurses or public health officers who had MSc/MPH degrees will be selected for data collector supervisors. The data will be collected at baseline and at the end of 1 year of the intervention.

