### Data analysis

Descriptive statistics will be used to summarize the baseline data. A chi-square test will be performed to compare the baseline characteristics of the intervention and control groups. Comparisons of detection rate, diagnosis delay, and costs of TB care between and within the intervention and control groups will be done using independent samples and paired sample *t*-tests, respectively. The independent *t*-test will be also used for the knowledge and attitude of post-test results of practitioners.

Logistic regression analysis will be used to determine the factors associated with case detection rate and diagnosis delay. A univariable logistic regression model will be fitted, and variables having a *p*-value less than 0.25 in the univariable logistic regression model will be fitted into the multivariable models. Variables with a *p*-value < 0.05 in the multivariable logistic regression model can be considered statistically significant. Crude and adjusted odds ratio (OR) with 95% confidence interval (CI) will be calculated to measure the strength of association between the dependent and independent variables. The fitness of the logistic regression model will be checked using the Hosmer–Lemeshow goodness of fitness test at *p*-value > 0.05. Multicollinearity between explanatory variables will be checked by a variance inflation factor (VIF), and variables with a VIF > 5 will be excluded from the final models.

Generalized linear mixed models (GLMM) will be used to assess the impact of the intervention on the change of cost of TB care. This GLM enables us to accommodate the correlation of observations due to the pre and post-intervention measurements and clustering of individuals within randomly selected clusters. Model fitting will be checked before the analysis is done. The effects of potential confounding factors will be controlled. The variance of the cluster-level residual errors will be computed using the intercept-only model. The variation between and within the groups will be analyzed.

Subgroup analysis will be employed to explore whether there is evidence that the detection variation depends on certain patients or facility characteristics. Covariate adjusted analysis will also employ to refine the analysis of case detection variation in the intervention and control arms the fact that some baseline characteristics may be related to outcome and unbalanced between the groups.

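### Diagnosis delay and catastrophic cost are sized for one two-proportion comparison, but parts of the protocol conclude on a baseline-to-end-line change between arms, for which the stated 80% power is not delivered

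*Protocol article*

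**What the plan says.** **How the two outcomes were sized.** The sample size section for diagnosis delay states that "the sample size will be calculated using the two-sample comparison of proportions formula in STATA version 16". It starts from "proportion of diagnosis delay P1 = 59.9"% and assumes a 14-point fall to 45.9%, with 80% power, 5% type 1 error and 10% non-response. This gives 438, then 416 (208 per arm) after a 0.95 multiplier. The section on cost repeats the method ("The sample size will be calculated by using the two-sample comparison of proportions formula using STATA version 16") with 40% against 27%, giving 453 and then 428 (214 per arm). Neither calculation contains a baseline round, a change, or a pre/post correlation.

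**What will be compared.** Several places describe a change:
- Phase 4, which sets the two arms against each other: "The comparison will be done between the end-line and baseline outcomes (case detection rate, cost of TB, and diagnosis delay").
- Control groups: "changes between the two groups will be assessed and concluded".
- Data analysis, on the mixed model: it "will be used to assess the impact of the intervention on the change of cost of TB care".

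Other places describe a comparison between arms. The abstract has a mixed model between arms adjusted for baseline differences. Data analysis has independent-samples t-tests between arms, alongside paired t-tests within arms, and it names no change model for delay.

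**When data are collected.** "The data will be collected at baseline and at the end of 1 year of the intervention". The protocol does not say whether 416/428 is the number at each round or over both.

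**The concern.** A change compared between arms is a difference of two differences. If the rounds contain different patients, it is built from four independent proportions instead of two, and its sampling variance is about twice what the sizing formula assumes. The 80% would then belong to one planned comparison while the Control groups section draws its conclusion from another. A real 13- or 14-point reduction would be missed about half the time, and a null result on a secondary outcome could be over-read as absence of effect. The mismatch is separate from the 0.95 multiplier: correcting the multiplier alone would leave it in place.

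**Working it through.** **Inputs.** P1 and P2 are 59.9% and 45.9% (delay), 40% and 27% (cost). Alpha is 0.05, taken as two-sided because a 95% CI is named. Final numbers are 208 and 214 per arm. There are three districts per arm (Randomization and recruitment). Assumptions of this check: the control proportion stays at P1 in both rounds, and the ICC, where used, is 0.05, the between-centre value in the sample size sections.

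**1. Reproduce the plan.** n per arm = [1.96·√(2p̄(1−p̄)) + 0.842·√(P1(1−P1)+P2(1−P2))]² / (P1−P2)²
- Delay: 3.888/0.0196 = 198.4, so 199; 398 in total; × 1.1 = 437.8 (printed 438); × 0.95 = 416 (printed 416).
- Cost: 3.477/0.0169 = 205.7, so 206; 412 in total; × 1.1 = 453.2 (printed 453); 453 × 0.95 = 430 (printed 428).

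The printed sizes are therefore those of a single-time-point comparison. Its power at 208 and 214 per arm, with full response and no clustering, is about 82% for both outcomes.

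**2. Can the rounds share patients?** Patients enter once TB is confirmed and registered (Randomization and recruitment), and baseline data precede the intervention (Phase 2). Delay runs from symptom onset to diagnosis, so it is already fixed at entry. Catastrophic cost is one total from symptom onset to the end of treatment (Appendix 2). Neither can be measured again a year later as a response to the intervention, so the rounds must be different people.

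**3. Power of the change contrast, no clustering.** SE = √[(3·P1(1−P1) + P2(1−P2))/n], with n per arm per round; power = Φ(d/SE − 1.96), d = P1 − P2.
- Delay: numerator 3 × 0.2402 + 0.2483 = 0.9689, against 0.4885 for the end-line comparison (ratio 1.98). With n = 208, SE = 0.0683, d/SE = 2.05, power 53.6%.
- Cost: numerator 3 × 0.2400 + 0.1971 = 0.9171, against 0.4371 (ratio 2.10). With n = 214, SE = 0.0655, d/SE = 1.99, power 51.0%.

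| Number per arm per round | Delay | Cost |
|---|---|---|
| 208 / 214 | 53.6% | 51.0% |
| 10% non-response (187 / 193) | 49.4% | 47.0% |
| 416/428 covers both rounds (104 / 107) | 30.5% | 28.9% |

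**4. With district clustering (ICC 0.05, m = n/3 patients per district).**
- End-line, unadjusted: design effect 1 + (m − 1) × 0.05 = 4.42 (delay, m = 69.3) and 4.52 (cost, m = 71.3). SE = 0.102 and 0.096; d/SE = 1.37 and 1.35. Power is 28% and 27% by normal approximation, 19% and 18% with 4 df (noncentral t).
- Change, district effects fully stable over time: variance × 0.95. SE = 0.0665 and 0.0638; d/SE = 2.10 and 2.04. Power is 56% and 53% (normal), 36% and 35% with 4 df. If district effects do not persist at all, the normal figures fall to 16% and 15%.
- End-line adjusted for district baseline, stable districts: the correlation of baseline and end-line district means is r = 0.05m/design effect = 0.785 and 0.790. SE × √(1 − r²) = 0.0631 and 0.0589; d/SE = 2.22 and 2.21. Power is about 34% for both with 3 df. This takes the covariate as balanced between arms; allowing for chance imbalance among six districts brings it to about 31% or a little lower.

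**The case against.** The strongest reply is that the plan does contain the comparison it was sized for. The abstract and the between-arm tests under Data analysis fit a single end-line contrast, and for delay Data analysis offers only t-tests and logistic regression. The Phase 4 and Control groups sentences are loosely worded and sit outside the analysis section. This stands: a reader might infer that the change is the only basis for the conclusion, and the documents do not support that. The protocol offers both contrasts, and has a power statement that fits only one.

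A second reply is that the paired t-tests and the pre/post correlation wording imply repeated measurement of the same patients. With an assumed correlation of 0.5, power for the change would return to 82.7% (delay) and 80.1% (cost). This does not stand, because both outcomes occur once per patient. The wording is a further inconsistency and does not rescue the power. Correlation between rounds within a district is possible, and step 4 allows for it.

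A third reply is that 51–54% cannot be a ceiling. A reader might take it as the best achievable, but that is not supported. The stable-district case gives 56% and 53% by normal approximation. The t-tests, and perhaps the cost model, treat delay and cost as continuous, and their power cannot be computed because no SD is given.

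A fourth reply is that moving to the end-line contrast does not recover 80% once three districts per arm are counted. This stands and shapes the fix.

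**Conclusion.** The point holds conditionally. The sample size sections fit one two-proportion comparison, while Phase 4 and Control groups (both outcomes) and Data analysis (cost) describe a between-arm change. If the conclusion rests on the change in the binary outcomes, power is about 54% for delay and 51% for cost instead of 80%. That assumes different patients in each round, full numbers at each round, an unchanged control proportion and no clustering. Non-response, splitting the total over two rounds, or district effects that drift lower it.

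It would be wrong to infer that the 80% is safe for the end-line comparison. Under an ICC of 0.05 with three districts per arm, that comparison has about 27–28% unadjusted (18–19% with 4 df). The baseline-adjusted and change contrasts have about 31–36% with stable districts and small-sample degrees of freedom. Adjustment therefore offers no clear power advantage over the change contrast here. The reason to prefer it is that it matches the abstract and gives one defined contrast. Both outcomes are secondary, so the primary outcome is not affected by this point.

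**What to change.** - In Phase 4, Control groups and Data analysis, name one contrast for delay and catastrophic cost: the end-line comparison between arms, adjusted for each district's baseline level, in line with the abstract. Label the difference in changes as descriptive.
- Remove the paired within-arm tests for these two outcomes, and confine any pre/post correlation in the mixed model to the district level. State that baseline and end-line patients are different people.
- In the two sample size sections, state that 208 and 214 per arm are end-line numbers.
- Withdraw the 80% for both contrasts. Restate power for the chosen one with district clustering and small-sample degrees of freedom, giving the ICC as an assumption with a range.

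**Cost.** Wording in a few sections, a much less favourable stated power, and one of the four between-district degrees of freedom for the baseline covariate. The baseline data are already to be collected, and no extra patients are needed.

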### Randomization and recruitment

Randomization will be done at the district level. There are thirteen districts and two town administrations. Among a total of districts and town administrations, six districts and/or town administrations in South Gondar Zone will be selected using the random.org software by considering the rule of thumb assumption that covers 40% of districts and town administrations. Thus, the selected districts/town administrations will be assigned to the intervention and control arms with a 1:1 allocation ratio. This means three districts or town administrations will be randomly assigned to the intervention arm, and the other three districts or town administrations will be assigned to the control arm. District or town size will not be considered in the randomization process. All health facilities in the intervention and control arms fulfilling the eligibility criteria will be included in the study. The eligibility criteria for the inclusion and/or exclusion of health facilities will be based on the availability of TB diagnostic and treatment services, including the microscope diagnostic service and DOT programs. Participants will recruit to the study when confirmed they have any form of TB and are registered to the DOT programs. Participants will enter into the trial individually based, and patients will recruit continuously until the desired sample size achieve. Recruitment of participants will be from July 1 to September 30, 2022. The statistician who allocated the intervention and control arms, an expert who assesses the outcomes, participants who will be assigned to intervention and control arms, and healthcare providers who provide TB care will not be aware of who were assigned to the intervention and control arms. The project manager and/or investigators will be unblinded.

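### Diagnosis delay and catastrophic cost are sized with a 0.95 multiplier for individual randomisation, although whole districts are randomised, so the stated 80% power is not delivered

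*Protocol article*

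**What the plan says.** The abstract, the section on study design and participants, and the discussion all describe a cluster randomised trial. The section on randomization and recruitment is explicit: "Randomization will be done at the district level". Six districts or town administrations are drawn and allocated 1:1, three to each arm.

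The sample-size section for diagnosis delay takes a different design: "Since the study is a multicenter, individually randomized trial, the design effect will be used". It starts from a "proportion of diagnosis delay P1 = 59.9"% in the control arm and, "as compared to the control, P2 = 45.9"% in the intervention arm. It then gives "power of 80%, and a 10% non-response rate, the total sample size will be 438". Randomisation is taken to be stratified on centres, and "assuming the variation between the centers will be 0.05", the total is multiplied by 1 − ρ = 0.95 to reach 416 (208 per arm).

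The section for cost of TB care follows the same route from 40% versus 27%, and ends with "the final sample size will be calculated as sample size * design effect 453 * 0.95 = 428" (214 per arm).

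The section for the TB detection rate uses a different formula, one that inflates for clustering. It has an ICC of 0.03 and an average of 18 individuals per cluster, and it reports 40 clusters, 24 in the intervention arm and 16 in the control arm.

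**The concern.** The two descriptions of the design cannot both be true. A district that lies wholly in one arm cannot be a stratum within which patients are randomised to both arms.

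The choice fixes the direction of the correction. If both arms are present in every centre, differences between centres cancel out of the treatment comparison, and a factor slightly below 1 is right. If whole districts are allocated, differences between districts become part of the error of that comparison, and the factor exceeds 1. The protocol took the first factor for the second design.

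Delay and cost are secondary outcomes, but they are two of the three specific objectives, and theirs are the only calculations that state a power. A reader who meets a non-significant result on either would weigh it against 80% power that the design does not have.

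**Working it through.** **Inputs.** From the two sample-size sections: 59.9% versus 45.9% (delay), 40% versus 27% (cost), type I error 0.05, power 80%, 10% non-response, ρ = 0.05, final 208 and 214 per arm. From randomization and recruitment: three districts per arm. From the detection-rate section: ICC 0.03 as an alternative. Assumed: a two-sided test (sidedness is not stated, but this reproduces the protocol's totals), equal district sizes, and an end-line comparison without baseline adjustment.

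**Step 1: reproduce the plan's figures.** Per arm, n = [1.96·√(2p̄(1 − p̄)) + 0.8416·√(p₁(1 − p₁) + p₂(1 − p₂))]² / (p₁ − p₂)².

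- Delay: p̄ = 0.529; n = (1.3836 + 0.5882)² / 0.0196 = 198.4, so 199. Total 398; × 1.10 = 438. This matches.
- Cost: p̄ = 0.335; n = (1.3083 + 0.5564)² / 0.0169 = 205.7, so 206. Total 412; × 1.10 = 453. This matches.
- 438 × 0.95 = 416.1, which matches. 453 × 0.95 = 430.35, whereas 428 is printed.

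The starting figures are sound for individual randomisation. The fault enters at the multiplier.

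**Step 2: the factor for district allocation.** DE = 1 + (m − 1)ρ, with m the patients per district.

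- Delay: m = 208/3 = 69.3; DE = 1 + 68.3 × 0.05 = 4.42; effective n = 208/4.42 ≈ 47 per arm, against 199 needed.
- Cost: m = 214/3 = 71.3; DE = 1 + 70.3 × 0.05 = 4.52; effective n = 214/4.52 ≈ 47 per arm, against 206 needed.

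**Step 3: power.** SE = √[(p₁(1 − p₁) + p₂(1 − p₂)) / effective n]. For delay at ρ = 0.05, SE = √(0.4885/47.1) = 0.102, and 0.14/0.102 = 1.37. The normal approximation gives Φ(1.37 − 1.96) = 28%. Six randomised districts leave 6 − 2 = 4 df, and a noncentral t gives 19%. Repeating this:

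| ρ | Delay, normal / t (4 df) | Cost, normal / t (4 df) |
|---|---|---|
| 0.05 | 28% / 19% | 27% / 18% |
| 0.03 | 38% / 25% | 37% / 24% |
| 0.01 | about 60% / 40% | about 60% / 39% |

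Using the pooled null variance in the normal approximation lowers these figures by about one point at most.

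**Step 4: can more patients help?** As m grows, effective n per arm approaches 3/ρ.

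- At ρ = 0.05 this limit is 60, below the 199 or 206 needed. Equivalently, 199 × 0.05 = 9.95 and 206 × 0.05 = 10.3 both exceed the three districts available. The power ceiling is 33–34% (normal) or 22% (4 df).
- At ρ = 0.01 the limit is 300, above what is needed. The normal-approximation ceiling is then about 93%.

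**Step 5: detectable difference.** At ρ = 0.05 with 4 df, 80% power needs a difference of about 36 percentage points for delay and 31 for cost, against the planned 14 and 13.

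**The case against.** **The power figure is conditional.** A reader might infer that the true power is simply 20–30%. The documents do not fix that. They give no district-level ICC; the 0.05 is described as variation between centres, and a centre may well be a health facility. Baseline data are also to be collected, with adjustment for baseline differences, and that could remove some between-district variance by an amount the protocol does not let us compute. This stands, and it is why a range is given. It does not restore 80%: even ρ = 0.01 gives only about 60%, or 39–40% with 4 df. The table assumes equal districts, whereas the protocol says size is ignored in randomisation; unequal sizes would lower power.

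**The claim that no number of patients would suffice** is likewise limited to the larger ρ values. Under the normal approximation it fails at ρ = 0.01.

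**The protocol does contain a cluster inflation.** Its detection-rate formula with n = 214, a 0.25 variation term, m = 18 and ICC 0.03 gives 214 × [1 + (1.25 × 18 − 1) × 0.03] / 18 = 214 × 1.645 / 18 = 19.6, so 20 per arm and 40 in all. One might infer that 428 was an input to this step and that 40 × 18 = 720 patients were intended. The protocol does not state n there, and the heading and ICC concern the detection rate, so this is only a conjecture. If 24 and 16 clusters were the randomised units, with 720 patients, power for delay would be about 82% at ICC 0.03 and 73% at 0.05 (normal approximation). With the stated 416 patients it would be about 72% and 66%. But the randomised unit is the district, and facilities inside a district add no randomised units. The 1 − ρ multiplier would be wrong for 40 allocated clusters too.

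**The remark about more than ten centres.** It is tempting to say the trial has only six. That equates centres with districts, which the protocol does not establish, since all eligible facilities in the six districts take part. The valid objection is that no centre contains both arms.

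**Conclusion.** The concern holds as a contradiction between the stated design and the sample-size method for two secondary outcomes. The 0.95 multiplier belongs to a design the trial does not use, and it moves the sample in the wrong direction.

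On an unadjusted end-line comparison with three equal districts per arm, power runs from 18–28% at ρ = 0.05 to 39–60% at ρ = 0.01, depending on ρ and on whether the 4 df are respected. It is below 80% throughout. Which figure applies depends on a district ICC that the protocol does not give. The point says nothing about power for the primary outcome, the case detection rate, for which no power is stated.

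Two further items are certain: the product 453 × 0.95 is misprinted by two patients, and 24 versus 16 clusters does not agree with three versus three districts.

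**What to change.** - In both the delay and the cost calculations, remove the description of the trial as individually randomised and the 1 − ρ multiplier, together with the assumption of stratification on centres.
- Use 1 + (m − 1)ρ with the district as the randomised unit.
- Reconcile the 40 clusters in the detection-rate section with the six districts in randomization and recruitment, saying what a cluster is in each place.
- In place of 80%, state the achieved power and the detectable difference for delay and catastrophic cost over ρ = 0.01 to 0.05, noting the small number of randomised units.
- Correct 428, which should read 430 if the product is shown at all.

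This changes protocol wording only and needs no extra patients. The cost is a much less favourable stated power for both outcomes.
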